## Abstract

**Background:**

The behavioural impact of pharmacogenomics is untested; informing smokers of genetic test results for responsiveness to smoking cessation medication may increase adherence to this medication. The objective of this trial is to estimate the impact upon adherence to nicotine replacement therapy (NRT) of informing smokers that their oral dose of NRT has been tailored to a DNA analysis. Hypotheses to be tested are as follows:

I	Adherence to NRT is greater among smokers informed that their oral dose of NRT is tailored to an analysis of DNA (genotype), compared to one tailored to nicotine dependence questionnaire score (phenotype).

II Amongst smokers who fail to quit at six months, motivation to make another quit attempt is lower when informed that their oral dose of NRT was tailored to genotype rather than phenotype.

**Methods/Design:**

An open label, parallel groups randomised trial in which 630 adult smokers (smoking 10 or more cigarettes daily) using National Health Service (NHS) stop smoking services in primary care are randomly allocated to one of two groups:

i. NRT oral dose tailored by DNA analysis (*OPRM1 *gene) (genotype), or

ii. NRT oral dose tailored by nicotine dependence questionnaire score (phenotype)

The primary outcome is proportion of prescribed NRT consumed in the first 28 days following an initial quit attempt, with the secondary outcome being motivation to make another quit attempt, amongst smokers not abstinent at six months. Other outcomes include adherence to NRT in the first seven days and biochemically validated smoking abstinence at six months. The primary outcome will be collected on 630 smokers allowing sufficient power to detect a 7.5% difference in mean proportion of NRT consumed using a two-tailed test at the 5% level of significance between groups. The proportion of all NRT consumed in the first four weeks of quitting will be compared between arms using an independent samples *t*-test and by estimating the 95% confidence interval for observed between-arm difference in mean NRT consumption (Hypothesis I). Motivation to make another quit attempt will be compared between arms in those failing to quit by six months (Hypothesis II).

**Discussion:**

This is the first clinical trial evaluating the behavioural impact on adherence of prescribing medication using genetic rather than phenotypic information. Specific issues regarding the choice of design for trials of interventions of this kind are discussed.

**Trial details:**

Funder: Medical Research Council (MRC)

Grant number: G0500274

ISRCTN: 14352545

Date trial stated: June 2007

Expected end date: December 2009

Expected reporting date: December 2010

## Background

Adherence to nicotine replacement in smoking cessation is widely perceived to be problematic; educating smokers about nicotine replacement use with generic or tailored feedback does not readily alter behaviour [1,2]. There are, however, high expectations of the potential for DNA-based risk information to motivate behaviour change more strongly than other types of risk information [3-5]. Such expectations are consistent with theories of attitude change which predict that the greater the personal salience of information, such as information regarding one's own DNA, the greater its impact [6]. We present here a protocol for a randomised controlled trial assessing the impact on adherence of prescribing a tailored oral dose of nicotine replacement therapy (NRT) based on genotype assessing smokers' receptivity to nicotine, compared with a prescription tailored on nicotine dependence (phenotype). The behavioural effect will be measured by the proportion of all prescribed NRT consumed.

It is well-established that both the initiation and maintenance of smoking have high heritability [7-9]. There is also growing evidence that some of the variability in responsiveness to smoking cessation pharmacotherapy, such as NRT or bupropion, is explained by genotype [10-12]. The Asn40Asp (A118G) polymorphism (rs1799971), found in exon I of the *OPRM1 *gene, has been associated with functional changes in mu-opioid receptors [13]. This mis-sense SNP leads to the substitution of an asparagine (Asn) for an aspartate (Asp) at position 40 in the amino acid sequence. The Asp (G) allele has been shown to bind beta-endorphin three times more strongly than the Asn (A) allele [14], although two replication studies failed to find this [15,16]. The Asp (G) allele has also been associated with reduced expression of the receptor [16]. Thus, for example, smokers with a particular variant in the mu-opioid receptor (*OPRM1*) gene (Asp40, present in about 25% of the population) that regulates the binding affinity of beta-endorphins, have been reported to show double the short term quit-rates when using a form of NRT with higher levels of replacement compared with NRT that results in lower levels of replacement [17]. Those homozygous for the more common variant (Asn40) were equally likely to stop smoking regardless of the level of NRT replacement. These results support the hypothesis that smokers with one or more copies of the Asp40 variant are more likely to stop smoking following higher doses of NRT than are smokers without this variant. Although this association was not replicated in a more recent study [18], the earlier research provides face validity for an exploration of the motivating impact of such DNA based information on smoking cessation.

Genetic tests are now available via the Internet (e.g. Respiragene http://www.synergenz.com), which, it is claimed, may be used to identify the optimal pharmacotherapy for an individual wishing to stop smoking or motivate an individual to stop smoking. The impact of such testing on smoking cessation behaviour is currently unevaluated but it has the potential to increase quit rates in two key ways. Firstly, by more effective prescribing i.e. prescribing that is tailored to the individual's nicotine metabolism to avoid over-prescribing with consequent lack of adherence or under-prescribing with consequent urges to smoke; and secondly, by increasing expectations of treatment effectiveness, and hence motivation to comply with the treatment. The focus of the current trial is upon the latter. There is growing evidence to suggest that perceiving a health problem to have a genetic cause increases the perceived effectiveness of taking medication to deal with the problem [19]. This has been documented for depression, heart disease and stopping smoking [20-23]. Given perceived treatment effectiveness predicts treatment use, tailoring treatment on the basis of genetic testing has the potential to improve treatment outcomes by increasing adherence. These observations inform the scientific rationale and principal hypothesis for the current trial.

A preliminary study suggests that prescribing based on genetic testing has the potential both to facilitate cessation by increasing the attractiveness of effective pharmacological treatments, as well as to undermine it, by decreasing the perceived importance of willpower in smoking cessation [23]. In this experimental analogue study, smokers who were asked to imagine that they had a gene variant that predicted a good response to bupropion, a medicine used to facilitate smoking cessation, were more likely to select the use of bupropion, the more effective treatment given their gene variant, to assist them in quitting. They were, however, less likely to perceive "willpower" as being important [23]. Other studies also report that medication is perceived as more effective when a condition is perceived as genetic [20-22]. In one such study, smokers who were randomised to receive feedback of genetic susceptibility to lung cancer perceived NRT as more helpful when quitting, compared to the group not receiving genetic feedback [24].

We predict that prescribing tailored to genotype increases adherence to NRT compared with prescribing tailored to phenotype, by strengthening the perceived effectiveness of the medication, a good predictor of adherence [25]. Consumption of NRT directly increases the likelihood of sustained smoking cessation; this being dose-dependent in that the more NRT consumed, the greater the chance of sustained cessation [26,27]. It is the most popular medication used in UK NHS clinics [28].

Furthermore, given the common representation of genes as deterministic, conferring immutable effects, it is important to document the impact of DNA testing for nicotine responsiveness in the longer term upon attributions for failure to quit smoking among those smokers who do not quit. Informing patients that their prescription is tailored to their genotype may have negative effects through engendering a sense of fatalism, which is associated with perceiving a genetic cause to a health problem [29]. Such fatalistic responses are predicted to result in reduced motivation in this group to make a future quit attempt (amongst those who fail to quit by six months).

### Objective and hypotheses

We will estimate the impact upon adherence to NRT of informing smokers that their oral dose of NRT has been tailored on the basis of DNA analysis.

The trial tests two hypotheses:

I	Adherence to NRT is greater among smokers who are informed their oral dose of NRT is tailored to an analysis of DNA (genotype), compared to one tailored to nicotine dependence (phenotype).

II Amongst smokers who fail to quit at six months, motivation to make another quit attempt is lower when informed that their oral dose of NRT was tailored to genotype rather than phenotype.

While the trial is not powered to assess long term behavioural outcomes related to smoking, prolonged abstinence is measured at six months post quit date.

## Methods/Design

### Trial Design (*see Figure *1)

**Figure 1 F1:**
[figure not shown]
**Trial flow diagram**.

An open label, parallel group, randomised controlled trial in which participants were randomly allocated on a 1:1 basis to one of two groups:

i. NRT oral dose tailored by DNA analysis, or

ii. NRT oral dose tailored by nicotine dependence score

### Study Setting

The trial is taking place in National Health Service (NHS) smoking cessation clinics in primary care. These provide a combination of weekly behavioural support and pharmacotherapy to assist smokers to quit. Participants are being recruited from 29 primary care practices in two English cities, Birmingham and Bristol.

### Participants

The sample will comprise 630 smokers using NHS stop smoking services within primary care. To be included, participants must be aged 18 years or older and a regular cigarette smoker who wants to stop smoking. A 'regular smoker' is defined here as someone who has smoked an average of 10 or more cigarettes per day (including roll-ups) over the preceding 12 months. They must also be able to give informed consent to participate as well as to be able to complete the study questionnaires, either alone or with assistance.

Exclusion criteria:

1. Cigar, pipe and oral tobacco users who do not also smoke 10 or more cigarettes per day.

2. Those who meet the criteria contra-indicating NRT use, as described in the Summary Product Characteristics, updated by recent MHRA guidance. Although not all forms of NRT are contra-indicated in pregnancy or lactation, the metabolism of nicotine changes and there remain concerns about safety in this group which include the avoidance of 24 hour patches as described in our protocol. Therefore pregnant or lactating women or those who plan to become pregnant during the course of treatment will be excluded.

3. Those with previous severe adverse reactions to NRT patch or to oral NRT.

4. Those currently taking either medication for smoking cessation that they are unwilling to stop taking medication with a known influence on smoking cessation that they should not stop (*e.g. *nortriptyline for depression).

5. Those who are non-English speakers.

6. Those deemed unsuitable for the study by their primary care physicians.

### Genetic testing

All participants will give a sample of either blood or saliva for genotyping, although the results are only used for tailoring dose of oral NRT and communicated to participants in the intervention group.

This trial tests for variants in the mu-opioid receptor gene, *OPRM1*. It is expected that about 75% will be homozygous for Asn40, with about 25% heterozygous or homozygous for Asp40 (i.e. need the higher dose of NRT) [18]. DNA will be extracted from blood using commercially available methods. From participants who do not want to have a blood test, DNA will be extracted from saliva. Briefly, DNA is extracted using a standard "salting out" technique [30]. For the genotyping of the *OPRM1 *A118G polymorphism, PCR is carried out using an allele specific, two-tube primer method. The reaction mixture contained 0.5 μM of each *OPRM1 *and control primer, approximately 150 ng of DNA, 200 μM dNTPs, 2 mM MgCl_2 _and 0.5 units of Taq polymerase in a final volume of 25 μl. After an initial denaturation step for 10 min at 95°C, thermocycling consisting of 30 cycles of 95°C for 20 sec, 68°C for 45 sec, 72°C for 30 sec. A final extension phase of 72°C is followed by cooling of samples to 4°C. PCR products are separated on a 1% agarose gel at 200 V for 30 min and visualised using ethidium bromide. In order for samples to be valid, a 750 bp control product has to be formed in both allele specific reactions. A homozygote is indicated by the presence of a 561 bp product in one of the reactions and a heterozygote is represented by a 561 bp product in both of the reactions.

A greater than 95% success rate is expected for the extraction and amplification of DNA. In the event that DNA is not collected or laboratory procedures fail to extract and amplify the DNA from the sample, the participant will be asked to provide a further sample.

### Trial medication

The trial will take place in the context of NHS stop smoking services, which provide behavioural support and medication to assist smoking cessation. At the time that this trial started, more than 70% of smokers in these clinics used nicotine replacement therapy (NRT) [28]. Current best practice is to use NRT in combination with behavioural support [31,32]. Smokers in the current trial will all be prescribed NRT patches plus oral NRT 'top-up' medication, which is approximately 35% more effective than NRT patch alone [33]. NRT patch dose will be tailored in the same way in both arms of the trial, namely according to how many cigarettes are smoked per day. Oral NRT dose will be determined on a different basis in each arm of the trial: those in the genotype arm will have the dose tailored according to the *OPRM1 *variant that they carry; those in the phenotype arm will have the dose tailored according to their nicotine dependence. Details of the basis for these prescriptions are presented below. The aim of treatment is to continue with full dose NRT for the first four weeks after the quit day, after which medication is reduced, according to patient need.

### Interventions

All participants are to be offered behavioural support and nicotine replacement therapy. The intervention to which participants are randomised comprises the communication that their dose for oral NRT treatment is based on either genotype or phenotype.

#### Support for behavioural change

This is based on withdrawal orientated therapy [34] and is provided for all participants twice prior to quit day and weekly thereafter until four weeks after quitting and then once more eight weeks after quitting. All nurses have been trained to give behavioural support to NHS standards [35]. The support lasts 10-30 minutes, depending upon progress and stage of the quit attempt.

#### NRT patch prescription

All participants smoking 15 or more cigarettes per day are prescribed 21 mg patches; those smoking 10-14 cigarettes per day will be prescribed 14 mg patches.

#### Oral NRT prescription

All participants will be offered additional oral nicotine replacement (gum, microtabs, lozenges, or inhalator) with the choice of delivery system left to personal preference. The dose of oral NRT prescribed is based on delivered dose. Thus, a 2 mg gum delivers about 1 mg of NRT into the circulation, and a 10 mg inhalator cartridge delivers about 3 mg of NRT.

##### i. Genotype arm (Intervention)

Participants will be informed that their oral dose of NRT is based on their genetic test result, using the following script:

*"Your extra NRT is based on the results of a genetic test. We did a genetic test on the blood sample that you gave last week. People have different versions of the 'OPRM1' gene. This gene influences how dependent you are on nicotine. There is more information on genes in the leaflet. Based on the results of your genetic test, you are more likely to be successful in stopping smoking if you have a (**standard dose/higher dose**) of extra NRT. Recent research shows that people with your genetic test result are more successful at stopping smoking if they take all of the extra NRT, as well as using their patch*.

You should wear a new patch for 24 hours each day for at least four weeks. The patch works by releasing a steady dose of nicotine into your blood stream. You have also been given a **(dose/high dose) **of extra NRT. Please use this as well as wearing the patch. You may wish to take it when you get a craving, but you can also take it at other times of the day. Even if you feel you don't need the extra NRT, you should take it. Many quit attempts fail because people don't take enough NRT or stop taking it before they have beaten their withdrawal symptoms. Remember that this dose has been calculated to suit your individual needs - try to stick to this amount each day in addition to wearing the patch."

Participants with the Asn variant will be advised to take additional NRT equivalent to the delivery of 6 mg of NRT a day. Those with the Asp variant will be advised to take additional NRT equivalent to delivery of 12 mg a day. A rationale booklet will be given to each participant describing:

i. their personalised additional oral dose of NRT based on their genetic test result. Participants with the Asn variant will be informed that they need a standard dose of additional NRT and participants with the Asp variant will be informed that they need a higher dose of additional NRT;

ii. the basis upon which this dose was calculated (*ie *a genetic test to establish which version of the "*OPRM1*" gene they carry);

iii. information about genes;

iv. information about the amount of additional NRT they should take in addition to wearing a new patch every day for at least 4 weeks;

v. the physiological mechanisms by which wearing their NRT patch and taking all their personalised dose of additional NRT each day for four weeks increases their chances of stopping smoking.

##### ii.	Phenotype arm (Comparison)

Participants will be informed that their oral dose of NRT is based on their nicotine dependence scores from questionnaire answers, using the following script:

*"Your extra NRT is based on the results of the questionnaire you completed last week. The questionnaire shows how dependent you are on nicotine. Based on the results of this questionnaire, you are more likely to be successful in stopping smoking if you have a (**standard dose/higher dose) **of extra NRT. Recent research shows that people who got this score on the questionnaire are more successful at stopping smoking if they take all of the extra NRT, as well as using their patch*.

You should wear a new patch for 24 hours each day for at least four weeks. The patch works by releasing a steady dose of nicotine into your blood stream. You have also been given a (**dose/high dose**) of extra NRT. Please use this as well as wearing the patch. You may wish to take it when you get a craving, but you can also take it at other times of the day. Even if you feel you don't need the extra NRT, you should take it. Many quit attempts fail because people don't take enough NRT or stop taking it before they have beaten their withdrawal symptoms. Remember that this dose has been calculated to suit your individual needs - try to stick to this amount each day in addition to wearing the patch."

Participants scoring less than 7 on the Fagerström Test for Nicotine Dependence (FTND - [36]) are categorised as low dependence and those scoring 8 or above as high dependence. It is estimated that approximately 25% of the sample will score 7 or higher on the FTND [37]. Drawing on usual practice in which dose is proportional to smoking burden [38], those in the low dependence group will be advised to take an additional amount of top up to deliver 6 mg of NRT. Those in the high dependence group will be advised to take an additional amount equivalent to 12 mg of NRT delivered a day.

Planned interim analysis (overseen by the Trial Steering Committee) including the first 160 participants revealed a substantial difference between the number of participants that obtained the higher dose of additional NRT in the phenotype arm (n = 32) compared to the genotype arm (n = 14). In order to balance the higher and lower dose oral NRT in the two arms, a cut-off of 8 rather than 7 on the FTND will be used for the remainder of recruitment.

A rationale booklet will be given to each participant, describing:

i. their personalised additional oral dose of NRT based on their questionnaire responses. Participants who score less than 8 (or 7, prior to an interim analysis) on the FTND are informed that they need a standard dose of additional NRT; participants who score above the cut-off are informed that they need a higher dose of additional NRT;

ii. the basis upon which this dose was calculated (*i.e. *responses to a questionnaire, revealing how dependent they are on nicotine);

iii. information about the amount of personalised additional NRT they should take in addition to wearing a new patch every day for at least 4 weeks;

iv. the physiological mechanisms by which wearing their NRT patch and taking all their personalised dose of additional NRT each day for four weeks increases their chances of stopping smoking.

### Procedure

#### Participant recruitment

Smokers listed on the databases of participating general practices will be written to inviting those wanting to stop smoking to come into the trial. Those interested will be invited to contact a research nurse to arrange to attend a clinic at their general practice run by the research nurse.

#### Consent process

Those wishing to participate will be asked to sign the study consent form. Blood will be taken for DNA testing from both groups and the baseline questionnaire will be completed. A time will be arranged for the nurse to telephone to confirm participation and attendance at the next clinic visit. Those confirming participation will then be randomized.

#### Data collection

Participants will be asked to attend seven weekly clinic sessions. In the first clinic participants will complete a baseline questionnaire. NRT will be prescribed according to the protocol at the second clinic visit and a quit date agreed. All participants will be given a small card summarising their top up dose of NRT and describing the rationale for this, which will vary according to whether it is tailored by DNA analysis or nicotine dependence. In the third clinic a second questionnaire will be completed. Participants are requested to continue to take their NRT as prescribed for four weeks post quit attempt and to attend weekly clinic visits. All participants will be contacted six months after their quit dates to assess the study endpoints by questionnaires sent by post or administered by telephone.

### Outcomes

#### Hypothesis I

##### i) Primary outcome

The primary outcome is adherence to a 28-day prescription expressed as the proportion of all NRT prescribed (in milligrams) that is consumed each day in the first four weeks of quitting, averaged over the four week quit period.

The proportion consumed will be measured by self-report daily diary, backed up by pill counts. If pill counts are discrepant with the diary, this will be discussed and reconciled by the research nurse at the weekly clinic visit. The adherence proportion on any day is the ratio of the amount of NRT consumed to the amount prescribed. The denominator of the amount prescribed derives from both NRT patch and top up. For example, for someone prescribed 1 × 21 mg patch and 6 × 1 mg oral NRT doses (equivalent to 6 × 2 mg gums, for example), the denominator is 27 mg. Consumption of the prescribed top ups and any additional top ups taken will count towards the total NRT consumed on a day. Wearing the patch for 24 hours a day will count as the maximum amount of NRT mg prescribed as having been consumed from the patch. If the patch is worn for a fraction of the 24 hours (such as 12 hours) then this fraction of the total NRT mg from the patch will be counted as having been consumed (such as 0.5 × 21 mg for a 21 mg patch worn for 12 hours), pro-rata. If the patch is not worn for 24 hours a day but additional oral NRT is taken then this will count towards the total NRT consumed on that day. For example, if someone prescribed a 21 mg patch and 6 mg of oral NRT, wears their patch for 16 hours a day and uses an additional 7 pieces of gum to make up for the 7 mg of NRT lost by the patch coming off early, this will be treated as 100% adherence (i.e. they have consumed 14 + 6 +7 = 27 mg). NRT consumed above that prescribed on any day could occur through excess top up consumption and will be treated as a daily proportion of 100%. The daily proportion will be treated as 0% when no NRT is consumed, if, for example, a person has resumed smoking.

Data quality for the primary outcome will be categorised into two main categories as 'high' or 'lower' for analysis. High quality data consists of i) adherence data that are validated by both the self-report daily diary and the pill count at the clinic visit, or ii) data reporting the resumption of smoking, whereby the participant informs the research team that they abandoned their quit attempt and resumed smoking. 'Lower' quality data consists of all other permutations.

It is expected that the behavioural effects of the intervention may be stronger in the first week of the quit attempt as fewer participants will have resumed smoking. Therefore a further short-term outcome is adherence to NRT during the first 7 days of the quit attempt.

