#### Concealment

At the start of the trial the randomisation sequence in each stratum will be generated using randomly permuted blocks by the trial statistician and concealed from the trial coordination team, therapists and participants. The statistical team will be given a participant's study identification code and the stratifier data necessary for the participant's randomisation. The only other information sent will be the participant's date of birth which will allow, at study closure, the agreement between the sequence generated and that used in the trial to be confirmed to have been securely operated.

After assignment, participants' study arm will not be concealed from participant, nurse or researchers. This will include the nurses collecting the primary endpoint data as they are also delivering the intervention. However, group allocation will be concealed from the research team collecting secondary outcome data on self-reported smoking status.

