### Fidelity checks

All sessions in which the rationale for the prescription will be presented (*ie *the second session, one-week pre-quit) will be tape-recorded. During the recruitment phase of the trial, assessments of a subsample of randomly selected recordings will be conducted to assess the fidelity of intervention delivery. Subsequently, feedback will be provided to the nurses to optimise intervention delivery. In addition, a sub-sample of these recordings will be randomly selected and transcribed to assess fidelity to the clinical protocol. The tapes will be stored in a locked cabinet until the end of the trial and completion of this analysis. They will be accessible only to the study team.

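### Diary versus pill-count discrepancies in the primary outcome are settled by discussion with the unblinded nurse who delivers the intervention, with no stated rule for which source prevails

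*Protocol article*

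**What the plan says.** The Primary outcome section sets the method: "The proportion consumed will be measured by self-report daily diary, backed up by pill counts". It then states what happens when the two sources disagree: "If pill counts are discrepant with the diary, this will be discussed and reconciled by the research nurse at the weekly clinic visit".

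The Concealment section says that after assignment "study arm will not be concealed from participant, nurse or researchers", and adds: "This will include the nurses collecting the primary endpoint data as they are also delivering the intervention". Concealment is kept elsewhere: "group allocation will be concealed from the research team collecting secondary outcome data on self-reported smoking status".

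The hypothesis has a direction. The Background says: "We predict that prescribing tailored to genotype increases adherence to NRT compared with prescribing tailored to phenotype".

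The data-quality paragraph of the Primary outcome section grades data as 'high' if they are "adherence data that are validated by both the self-report daily diary and the pill count at the clinic visit", or if the participant has reported resuming smoking. Everything else is 'lower'. It does not say where a value belongs that disagreed at first and agreed only after discussion.

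**The concern.** The value analysed can be one agreed between two people who both know the allocation, one of whom delivers the message under test. Delivery of the message has to be open. Settling a conflict between two recorded sources does not have to be done with knowledge of the arm.

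If discrepancies were settled more leniently in one arm, the difference would enter the arm means and look like an effect of the genetic message. It could run either way: leniency in the genotype arm would inflate the effect, and stricter questioning there would hide it. The significance test cannot separate this from a true effect, and neither can the confirmatory bootstrap, which addresses the distribution of the outcome and not its measurement.

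**Working it through.** **Inputs from the article (Sample size calculation).** 315 per arm; target difference 7.5 percentage points; two-sided 5% test; within-group standard error 1.85 points; high users 50% and 65%, the rest uniform.

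**The plan's own figures.** With a share p at full use and the rest uniform on 0 to 1, the mean is p + (1 - p)/2.
- p = 0.50 gives 75.0% and p = 0.65 gives 82.5%. The difference is 7.5 points, as stated.
- The variance is p + (1 - p)/3 minus the squared mean. The SDs are 32.3 and 29.3 points, pooled 30.8.

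**SE of the between-arm difference.**
- From the stated SE: 1.85 x sqrt(2) = 2.62 points.
- From the stated mixture: 30.8 x sqrt(2/315) = 2.46 points.

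The stated 90% power for the t-test is not reproduced from these inputs (81.8% with the stated SE, 86.3% with the mixture). That is a separate matter and does not affect this point, so both SEs are carried forward. An observed difference of 1.96 x 2.46 = 4.8 to 1.96 x 2.62 = 5.1 points would be significant.

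**Effect of differential reconciliation.** The article gives no discrepancy rate, so the next two quantities are assumptions: f, the share of participants with a reconciled discrepancy, and s, the net difference between arms in how far reconciliation moves their 28-day adherence. The bias is b = f x s. With no true effect, the two-sided rejection probability is

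Phi(b/SE - 1.96) + Phi(-b/SE - 1.96).

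| f | s (points) | b (points) | b as share of 7.5 | Type I error (SE 2.62 to 2.46) |
|---|---|---|---|---|
| 5% | 5 | 0.25 | 3% | 5.1% |
| 20% | 5 | 1.0 | 13% | 6.7% to 6.9% |
| 20% | 10 | 2.0 | 27% | 11.9% to 12.9% |
| 20% | 15 | 3.0 | 40% | 20.9% to 23.1% |

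**What such shifts require.** Take a participant prescribed a 21 mg patch and 6 mg orally (27 mg).
- One patch-day credited or removed changes that week by 21/27/7 = 11 points, but the 28-day mean by only 21/27/28 = 2.8 points. A 28-day shift of about 11 points needs one such patch-day in each of the four weeks.
- If the pill count covers oral units only, these are 6/27 = 22% of the prescription. A 15-point shift would then need 15/22, or about two-thirds, of that person's oral NRT to be settled differently.

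**Scoring rules that limit the shift.** Daily adherence is capped at 100%, and at least half the sample are assumed to be high users, so many values cannot be moved up. The cap does not stop an over-reported diary being pulled down less firmly in one arm. Under Handling missing data in the primary outcome, non-attenders who report a return to smoking or cannot be contacted score zero for the rest of the period by fixed rule, which leaves nothing to reconcile. Both rules make the bottom row of the table less likely; neither rules it out.

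**The case against.** The lack of blinding is disclosed, and nothing in the article contradicts it. A rule of precedence between sources, the order of form entry and the content of the sensitivity analysis may all sit in a fuller protocol or an analysis plan that is not shown. This stands as a limit: the missing rule is shown for this article only. It does not dispose of the point, because the article itself names who settles a discrepancy, how and when.

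Other parts of the plan give some cover. Effects are estimated for each nurse with a heterogeneity test, data are graded by quality, and a sensitivity analysis is announced. A reader might infer that no analysis offers any protection, and that goes too far. The nurse analysis could expose bias that differs between nurses, though not bias they share. The sensitivity analysis is announced under missing data without content. The fidelity recordings cover only the pre-quit session and not the visits where discrepancies are settled.

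Two stronger readings are tempting. One is that reconciled data will pass as 'high' quality. The data-quality paragraph does not say so, and its residual 'lower' category could equally take them. The other is that the nurse settles the discrepancy straight after urging full use of the NRT. The rationale is given one week before the quit date, reconciliation comes at later weekly visits, and the urging is nearly identical in both scripts. Only the stated basis of the dose differs by arm.

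It is also fair to say that diary and returned packs both come from participants who know their arm, so most self-report bias would survive any change to reconciliation. Nor does anything in the article place the concealed team at the weekly visits.

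**Conclusion.** The point holds as an avoidable exposure to bias in the primary outcome, and as something the plan should change. The procedure is stated, the person settling discrepancies knows the arm and delivers the intervention, and no safeguard described in the article removes a bias common to all nurses.

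The size is unknown and rests wholly on the assumed share and differential: from negligible (0.25 points, type I error about 5.1%) to material (3 points, 21-23%), with the upper end less likely for the reasons given above. A reader might conclude that a positive result would be an artefact, or that the bias must favour the genotype arm. The documents show neither: they give no discrepancy rate, no direction and no size.

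**What to change.** 1. Record the diary and the pill count in the case report form as first presented, before discussion, and flag each value changed by reconciliation.
2. Pre-specify a sensitivity analysis of the primary outcome on unreconciled data, derived without the arm code, in two versions: (a) the unreconciled diary; (b) the pill count limits the units used in each clinic interval, while the diary supplies the daily allocation and the patch wear-time. A pill count alone would not do, because the outcome averages daily capped proportions and counts patch hours pro rata.
3. Report the number and direction of reconciled changes by arm.
4. State in the data-quality paragraph that reconciled data are not graded 'high'.

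The cost is slightly more form entry and one extra analysis. No new assessor is needed. The article does not say that pre-discussion values are kept, so the form has to provide for them. Unreconciled values will carry somewhat more random error, and bias in participants' own self-report remains.
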